### Procedures

At the enrollment phase, families will be screened for inclusion criteria in a telephone interview (see Fig. 1). If the study requirements are met, the adolescents and their caregivers will be informed about the study procedures during an initial contact meeting and will receive the consent form. External randomization will be performed by a researcher who is not involved in the study. All patients will undergo an initial clinical assessment to determine clinical parameters (e.g., weight, height, BMI, pulse). The therapists will discuss the initial FBT-interventions with the family and, after randomization, inform the family whether they will additionally receive guidance for FBT-HT or FBT-MBSR. After the initial interview, both the adolescents and their parents will receive a web-based link to an electronic test battery assessing psychopathology and interfamily relationships to be completed within 7 days. The study intervention will last 3 months. At the end of the treatment phase, the clinical staff will again collect clinical parameters, and another link to an electronic test battery will be sent. During the 3-month treatment phase, weight, blood pressure, and pulse will be recorded weekly. In addition, treatment progress is to be assessed by both patients and therapists after each FBT consultation. After 12 months, families will be contacted by email and asked to complete the final test battery.

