### Power analysis

The target sample size for the primary analysis was derived from an a priori power calculation using G*Power (version 3.1.9.7) and repeated measures ANOVA as a statistical model. Assuming a small effect size of *f* = 0.2, power of 80%, type 1 error level of *p* < 0.05 and correlation among repeated measures of *r* = 0.5, the necessary total sample size of 66 is adequate to test our main hypothesis involving three groups, two time points and the statistical interaction term. Assuming a reasonable attrition rate of 25%, we set our target sample to 90, equivalent to 30 participants per group, assuming equal treatment arm sizes. This number also aligns with the study feasibility, as it approximates the number of eligible patients who previously registered at the outpatient clinic over time intervals similar to the planned recruitment period of 3 years.

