### Data analysis plan

The initial descriptive statistics will summarize participant data characteristics as means, standard deviations, minima, maxima, frequencies and percentages. The validity of stratified randomization will be evaluated by inspecting between-group differences at baseline by means of a one-way analysis of variance (ANOVA), Kruskall–Wallis test or chi-squared test (in dependency of conventional statistical assumptions and the variable type, i.e., continuous versus categorical). Outcome data will be evaluated for the normality assumption by a combination of visual (Q–Q plots, histograms) and statistical (Shapiro–Wilk test) methods and will be transformed if necessary to meet the normality assumption. Participant characteristics of the analyzed sample and dropouts will be subjected to an additional inspection for possible non-random differences. Missing data will be handled by the maximum likelihood estimation method. The effects of the interventions will be assessed as changes in the primary outcomes from pre-test to post-test and follow-up assessment using EDE, EDI-2 and BMI analyzed with a repeated measures ANOVA followed by a post-hoc Tukey’s test to compare treatment means when there is a significant effect. The potential influence of confounding factors (age, premorbid BMI, duration of illness, age at onset, duration and setting of pre-treatment, medication use) will be further explored in sensitivity analyses. The secondary continuous variables will be analyzed in parallel. The measures related to treatment implementation (FBB, BPT) will be evaluated using descriptive statistics. Corrected effect sizes, expressed as Hedges’s *g* and significant deviations beyond the 95% confidence interval, will be computed for between- and within-group terms and will indicate empirical power estimates for a subsequent confirmatory study. Exploratory analyses will test the FB-K measure as a mediator/moderator of efficacy. To examine the FBT process, the ratings of each therapy session by the adolescents and the therapists will be compared and analyzed to assess their common development over time. More advanced statistical methods, such as generalized estimating equations (GEE) (which allow for more flexible modelling of the correlation structure among observations, are less sensitive to violation of assumptions and estimate population-wide average effects) will be also applied to assess differences in BMI percentiles and EDE/EDI-2 trajectories. The statistical significance threshold will be set to *p* < 0.05.

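### The primary repeated measures ANOVA relies on equal change-score variances across visits at 0, 3 and 12 months; if correlation decays with time, 12-month contrasts on its pooled error can have about 8–11% false positives instead of 5%

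*Protocol article*

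**What the plan says.** The Data analysis plan defines the intervention effects as "changes in the primary outcomes from pre-test to post-test and follow-up assessment". The method it names for all three primary outcomes appears in the words "using EDE, EDI-2 and BMI analyzed with a repeated measures ANOVA". Comparisons between arms come after that model and are conditional on its result: it is to be "followed by a post-hoc Tukey’s test to compare treatment means when there is a significant effect". The significance threshold is 0.05.

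The visit times come from Procedures and Table 1 (Measures). "The study intervention will last 3 months", and the last assessment is at one year: "After 12 months, families will be contacted by email and asked to complete the final test battery". The visits are therefore week 0, week 12 and month 12, with gaps of about 3 and 9 months.

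The only distributional check stated for the outcomes concerns normality. Missing data are to be handled by maximum likelihood, with no covariance structure named. GEE is described as a method that would "allow for more flexible modelling of the correlation structure among observations", but it is applied in addition to the ANOVA and does not replace it.

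The Power analysis section sizes the main hypothesis on three groups and two time points, with f = 0.2, 80% power and one correlation, r = 0.5. No visit-specific correlations or SDs are given.

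**The concern.** A classical repeated measures ANOVA with three visits estimates one within-subject error and uses it for every comparison over time. This is right only under sphericity, meaning that baseline-to-week-12, week-12-to-month-12 and baseline-to-month-12 changes all have the same variance. With gaps of 3 and 9 months, a lower correlation between baseline and month 12 than between adjacent visits is a natural expectation. The 12-month change would then be more variable than the pooled error implies, and the week-12 change less variable.

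Two things would be at stake. A 12-month arm difference could be declared too often. The week-12 contrast, taken at the end of the 12-week add-on, would be tested against too large an error and lose power. A Greenhouse-Geisser correction would repair the omnibus F test but not visit-specific contrasts that still use the pooled error.

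**Working it through.** **1. The plan's own figure.** For the group-by-time interaction with k = 3 groups and m = 2 time points, λ = N·f²·m/(1 − r), on (k − 1)(m − 1) and (N − k)(m − 1) degrees of freedom. At N = 66, λ = 66 × 0.04 × 2/0.5 = 10.56 on 2 and 63 df, and power is 0.818. At N = 63 it is 0.798, so 66 is the first multiple of three to reach 80%. Then 66/0.75 = 88, rounded up to 90. The stated figure reproduces. With only two time points sphericity holds trivially, so this calculation does not touch the three-visit question.

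**2. Inputs for the check.** From the article: three arms, visits at 0, 3 and 12 months, alpha 0.05, 66/3 = 22 completers per arm. *Assumed*, because the article gives none: visit-specific correlations and SDs. Correlations are listed throughout as baseline–week 12 / week 12–month 12 / baseline–month 12.

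**3. Formulas.** The variance of a change is V = s₁² + s₂² − 2·r·s₁·s₂. The pooled error corresponds to the mean of the three change variances, V̄. The standard error used, relative to the correct one, is √(V̄/V). The pooled error has 2(N − 3) = 126 df; a contrast-specific error has N − 3 = 63.

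**4. Numbers.**

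| Assumed case | V (0–3) | V (3–12) | V (0–12) | V̄ | Week-12 SE | 12-month SE |
|---|---|---|---|---|---|---|
| 0.5/0.5/0.5, equal SDs | 1.0 | 1.0 | 1.0 | 1.0 | correct | correct |
| Mild: 0.5/0.5/0.3, equal SDs | 1.0 | 1.0 | 1.4 | 1.133 | √(1.133/1.0): +6% | √(1.133/1.4): −10% |
| Middle: 0.7/0.6/0.4, equal SDs | 0.6 | 0.8 | 1.2 | 0.867 | √(0.867/0.6): +20% | √(0.867/1.2): −15% |
| Strong: 0.8/0.6/0.4, SDs 1, 1.1, 1.3 | 0.45 | 1.184 | 1.65 | 1.095 | √(1.095/0.45): +56% | √(1.095/1.65): −19% |

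**5. Simulated consequences** (22 per arm, contrasts on the pooled error):

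- *One pair of arms, 12-month change, nominal 5%, no gate:* about 7.8%, 9.4% and 11% in the mild, middle and strong cases. With contrast-specific errors the rate is about 5% throughout.
- *Week 12:* the false-positive rate falls to about 4% (mild) and 2% (middle). For a true difference of 0.6 baseline SD, power is 58% instead of 72% (middle) and 46% instead of 83% (strong).
- *Omnibus interaction test:* about 5%, 6% and 7%.
- *Tukey family at 12 months, run only after a significant omnibus test, no effect at any visit:* about 4–7% over decaying-correlation cases.
- *Same gated procedure, one arm truly different at week 12 only (0.5 to 1.0 SD):* 7.8–11.4% for 0.5/0.5/0.3, 0.7/0.6/0.5 and 0.8/0.6/0.5 with equal SDs, because the real early effect opens the gate.

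**6. Patterns that do not follow the decay story** (ungated, three-arm comparison, week 12 then month 12):

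- 0.5/0.5/0.5, equal SDs: 5.1% at 12 months.
- 0.5/0.7/0.5, equal SDs: 7.4% and 7.5%, both inflated.
- 0.4/0.6/0.5, equal SDs: 8.2% and 5.1%, shifted to week 12.
- 0.5 throughout, SDs 1, 1.3, 1: 6.6% and 2.4%, reversed.

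**The case against.** The strongest reply is that several steps are inferred. The article does not state the error term for the Tukey comparisons, nor that all three visits enter one model; its power calculation uses two time points. The planned maximum likelihood handling could already mean a likelihood-based model, and its covariance structure, or a sphericity correction, may be set out in a full protocol or SAP that is not shown. The GEE would also help to expose a result that depends on sphericity. All of this stands as a limit on the claim: the silence on sphericity is not in itself a fault. What remains is that the article names repeated measures ANOVA as the main method for changes to both follow-up visits and puts the method with flexible correlation second.

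A reader might infer that the plan as written has an 8–11% false-positive rate at 12 months. The documents do not support that. The range comes from assumed correlations, and under the article's only value with equal SDs the rate is 5%. The plan also gates Tukey's test on a significant effect, which holds the rate near 4–7% when nothing differs at any visit.

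A reader might also infer a bias towards claiming lasting benefit. That does not follow either. An error that is too small inflates a two-sided test equally in both directions, and other covariance patterns move the problem to week 12 or reverse it.

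**Conclusion.** The point holds in conditional form. The named primary model, in its classical form, is valid for visit-specific change contrasts only under equal change-score variances, an assumption that unequally spaced visits make doubtful and that the article neither checks nor relaxes in the primary test. If correlation decays as in the mild to strong cases, pairwise 12-month contrasts on the pooled error run at about 8–11% when ungated. The gated procedure gives rates of similar size when a true week-12 effect opens the gate, and this case matters because the trial expects the add-on to work: a real short-term effect could be accompanied by a spurious 12-month difference. Week-12 power falls at the same time. These sizes rest on the assumed correlations and SDs, 22 completers per arm, and use of the pooled error for the contrasts. The change is worth making because it removes the dependence on all covariance patterns at little cost.

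**What to change.** Make the primary model a likelihood-based mixed model for repeated measures with arm, visit and their interaction, and an unstructured covariance over the three visits. Take the arm contrasts at week 12 and at 12 months from it, each with its own standard error, and use no pooled within-subject error for any contrast. Analysing each follow-up visit separately would serve the same purpose. The model fits the maximum likelihood handling of missing data already planned.

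The cost is a change of wording, a few more covariance parameters (six for three visits) and fewer error degrees of freedom per contrast (about 63 instead of 126 at 22 per arm). No additional data are needed.

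### The Tukey follow-up is tied neither to the group-by-time interaction nor to change; read as marginal treatment means, it tests average level with week 0 included

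*Protocol article*

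**What the plan says.** The Power analysis section takes a repeated measures ANOVA as its model and calls the resulting sample size "adequate to test our main hypothesis involving three groups, two time points and the statistical interaction term". The tested quantity is therefore the group-by-time interaction: whether the arms differ in how much they change. The Introduction makes the hypothesis pairwise, since FBT-HT is expected to do better than FBT alone and better than FBT-MBSR.

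The Data analysis plan opens the relevant sentence in line with this: "The effects of the interventions will be assessed as changes in the primary outcomes from pre-test to post-test and follow-up assessment". The sentence ends by saying that EDE, EDI-2 and BMI are "analyzed with a repeated measures ANOVA followed by a post-hoc Tukey’s test to compare treatment means when there is a significant effect". It gives no further definition of the effect that opens the Tukey step or of the means it compares. The same section also plans GEE models of trajectories, and Hedges's g with 95% confidence intervals.

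**The concern.** A three-arm interaction test has no direction and names no arm, so the pairwise hypothesis depends on the follow-up comparison. That comparison is loosely fixed in two respects.

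- **Trigger.** A repeated measures ANOVA yields a group effect, a time effect and an interaction. The text does not say which must be significant. Every arm receives weekly FBT, so a time effect is to be expected even if the arms do not differ, and it would satisfy the wording.
- **Quantity.** In this model, treatment means are ordinarily the marginal means of the between-person factor, averaged over visits. Table 1 of the article lists week 0 as one of those visits. A Tukey test on these means has equal average level as its null hypothesis, not equal change.

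Two analysts following the sentence could therefore test different null hypotheses with very different power. If the choice is left until the data are seen, the more favourable result could be picked.

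**Working it through.** **Inputs from the Power analysis section.** Three groups and two time points; "Assuming a small effect size of *f* = 0.2"; power 80%; "type 1 error level of *p* < 0.05"; "correlation among repeated measures of *r* = 0.5"; "the necessary total sample size of 66"; attrition 25%; target 90, or 30 per arm.

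**Step 1: reproduce the plan's figure.** For the within-between interaction, λ = f²·N·m/(1 − r), with (k − 1)(m − 1) and (N − k)(m − 1) degrees of freedom. With k = 3, m = 2 and N = 66, λ = 0.04 × 66 × 2 / 0.5 = 10.56 on 2 and 63 df. Power is 0.818; N = 63 gives 0.798. So 66 is the smallest multiple of 3 that reaches 80%, and the stated figure reproduces. Allowing for attrition, 66/0.75 = 88, which the plan rounds to 90.

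**Step 2: express f = 0.2 as an arm difference.** Assume FBT-HT exceeds two equal comparators by d after treatment, with no true difference at week 0 and unit SD at each visit. The change score has variance 2(1 − r) = 1, so λ = n·d²·(2/3). Setting 22 × d² × 2/3 = 10.56 gives d² = 0.72 and d = 0.85 SD.

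**Step 3: two visits, change against marginal mean.**

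- Change: difference d, variance 1, λ = 10.56.
- Mean of both visits: difference d/2, variance (1 + r)/2 = 0.75 (SD 0.866), so λ = 10.56 × 0.25/0.75 = 3.52.

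Noncentrality falls to one third, and omnibus power at N = 66 falls from 82% to 35%.

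**Step 4: three visits, effect fully kept at 12 months, r = 0.5 between all visits.**

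- Average post-baseline mean minus week 0: difference d, variance 0.75, λ = 10.56/0.75 = 14.08.
- Mean of all three visits: difference 2d/3, variance 2/3, λ = 10.56 × (4/9)/(2/3) = 7.04.

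Noncentrality is halved.

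**Step 5: Tukey power.** Simulation with 60,000 trials per setting, studentized-range critical value on 3(n − 1) df, FBT-HT against one comparator (against both in brackets):

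| Setting | On change | On marginal means |
|---|---|---|
| 2 visits, 22 per arm | 66% (51%) | 23% (11%) |
| 2 visits, 30 per arm | 82% (71%) | 32% (17%) |
| 3 visits, sustained effect, 22 per arm | 80% (69%) | 47% (30%) |
| 3 visits, sustained effect, 30 per arm | 92% (86%) | 62% (47%) |
| 3 visits, half the effect kept, 22 per arm | 52% (36%) | 26% (13%) |

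In the three-visit rows, change means the average post-baseline change.

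**Step 6: sensitivity.** With two visits, 22 per arm and d held at 0.85, power for one comparison is 49% on change against 27% on marginal means at r = 0.3, and 98% against 19% at r = 0.8. A Tukey test on the post-test means alone at r = 0.5 has the same power as on change (66%), so the loss arises only when week 0 is averaged in.

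**The case against.** The strongest reply is that the sentence should be read whole. It begins by saying that effects are assessed as changes, and the Power analysis section names the interaction. Together these point to a Tukey test between arms on change after a significant interaction, which has no power loss. The text nowhere says that the means are averaged over all visits. A condensed article may also leave such detail to the full protocol.

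Much of this stands. The marginal-means reading is one reading, and a reader who infers that the plan has definitely fixed the wrong test goes further than the text. But the article is not silent: it names the test, its target and its trigger, and the ordinary meaning of the target in this model conflicts with the start of the same sentence.

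Three other inferences are tempting and are not supported:

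- **That no other planned analysis can compare the arms.** GEE on trajectories and between-group Hedges's g with 95% intervals are also planned. The article names no pairwise arm contrast for the GEE, so Tukey remains the only arm-by-arm significance test it names for the primary outcomes.
- **That the Tukey step will usually miss a real effect.** With three visits, a sustained effect and 30 per arm, power for one comparison is 62% even on marginal means.
- **That false positives are inflated.** Tukey holds family error near 5% whatever opens the step, so a trigger met by a time effect does not raise it. Chance imbalance at week 0 does feed into marginal means, but it also affects unadjusted change scores, so it is not a defect of this method alone.

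**Conclusion.** The point holds as a badly fixed follow-up test. The trigger is not tied to the interaction, and the means are not tied to change, although both define the main hypothesis. If the means are taken as marginal treatment means, the test addresses level and loses about two thirds of its power for one comparison in the two-visit design on which the trial was sized (66% to 23% at 22 per arm). With three visits and a sustained effect it loses about 40% (80% to 47%). If the means are changes or post-test means, nothing is lost at r = 0.5.

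These figures assume one superior arm with d = 0.85 SD, two equal comparators, equal correlations of 0.5 between visits, and no true week-0 difference. The size of the loss depends on the reading and on these assumptions. The need to name the trigger and the contrast does not.

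**What to change.** Replace the end of the sentence with wording such as: *Only if the group-by-time interaction is significant are the arms compared further; the comparisons are Tukey-adjusted contrasts between arms of the week-0-adjusted mean (or of the change from week 0) at [named post-baseline visit]. Main effects of time or group do not trigger the comparisons.*

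The week-0-adjusted mean is the better choice. It deals with chance imbalance at week 0, and at r = 0.5 its residual variance is 1 − r² = 0.75 against 1 for change. This raises λ from 10.56 to about 14.08 at N = 66, ignoring the degree of freedom spent on the covariate.

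The cost is one sentence, with no extra patients or data. The Data Availability section states that no datasets exist yet, so the sentence can be settled before any outcome is seen.

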
## Conclusion

This study protocol builds on the hypothesis of FBT-HT functioning as a well-accepted and effective supplement to FBT [9, 17, 30]. By comparing FBT-HT to both standard outpatient FBT and FBT-MBSR, we can examine the extent to which the different treatment approaches differentially affect treatment outcomes as measured by (1) a change in BMI, (2) eating disorder psychopathology and (3) interfamilial stress experience and communication. We will also explore how different treatment arms are influenced by intrafamily relationships integrated as a mediator/moderator variable. Process analysis can be used to demonstrate how patients as well as therapists perceive (1) the therapy relationship, (2) therapy goal achievement and (3) therapeutic effect factors among the treatment arms. Accordingly, valuable insights with regard to the setting, frequency and therapy duration may be gained. As the responsibility for the therapy process is to be shared and there is to be ongoing exchange between the two therapists involved, we anticipate that the perceived burden on therapists will be lower in the combined groups (FBT-HT; FBT-MBSR). Further data analyses may also involve examining the influence of variables, such as clinical features (e.g., low body weight, high risk for inpatient referral), parental situation, number of siblings and occupation of parents, on the outcome of the different treatment modalities. As an additional consideration, one could also assess the indication for the corresponding treatment through baseline profiling [31]. Future studies will be relevant for more individualized treatment plans to optimize treatment outcomes. Finally, the proposed project is closely aligned with public health priorities to optimize the outcomes of evidence-based treatments and test their effectiveness in community-based settings, while collecting important contextual information to support implementation efforts.

## Data Availability

Data sharing is not relevant to this article because no datasets have yet been created or analyzed as part of this study.
